## Statistical methods

### Statistical methods for primary and secondary outcomes {20a}

The primary analysis will be an intention to treat analysis in which we will compare outcomes between all patients randomized to the two study arms, irrespective of whether they receive their allocated treatment. For the primary outcome of 30-day mortality, we will use the unadjusted hazard ratio determined from Cox regression to estimate the mortality rate ratio between the treatment groups. If we detect any imbalances in potential confounders at baseline (such as age, sex, severity of illness, study site), then an adjusted Cox model will be used. If losses to follow-up do occur, patients will be censored at time of last assessment. Kaplan-Meier survival curves will be constructed to display cumulative mortality over the 30-day follow-up period.

In the per-protocol analysis we will exclude patients stopping or pausing the study medication at any time point and those withdrawn from the trial.

Complete case analyses will be used for secondary endpoints. For all secondary endpoints, we will calculate unadjusted and adjusted estimates of the effect size and corresponding 95% confidence intervals using linear, logistic, or cox proportional hazards regression as appropriate. All analysis will be done using R (Version 4.4.2, R Foundation for Statistical Computing: Vienna, Austria)

For the immunology outcome, omics data such as proteomic and transcriptomic data generated will be processed in the R programming language as described in section 33. To find genes/proteins whose mean response has significantly changed over the first 72 hours, the processed data will be fitted in a multinomial mixed model predicting the possible outcomes, adjusting for relevant baseline characteristics. The expected outcomes are, survived versus died in the treatment and placebo arms.

To understand the biological response associated with survival, induced/repressed by the treatment, functional analysis of the significant genes/proteins will be explored using R packages such as Clusterprofiller, GSVA and fgsea.

Integrative approaches will be used on the cellular phenotyping, proteomic, transcriptomic, metabolomic data to elucidate the biological processes promoted/repressed by corticosteroid treatment that are associated with survival that could be targeted with additional intervention

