## Trial design {8}

We will conduct a pragmatic open label randomized controlled clinical trial. Eligible participants will be recruited from the in-patient adult medical wards of the participating hospitals. Patients admitted to the general wards as well as the High Dependency Units (HDU) and Intensive Care Units (ICU) will be eligible to join the trial and will be identified by the attending clinician and a study clinician.

Participants enrolled into the trial will be randomized 1:1 to either receive standard of care for CAP or standard of care plus a 10-day course of low-dose oral corticosteroids. A subset of all recruited participants, about 50 per trial arm, will be further randomized to have a blood draw at four timepoints during their participation. For these participants, a 10 ml blood sample will be collected at enrollment, 24, 48 and 72 hours after enrollment for an immunology sub study.

All participants will be followed up to their 30
^th^ day after enrollment to determine their vital status. The median duration of hospital admission for patients with CAP in the participating hospitals is 4 days, therefore having the primary outcome ascertained at 30 days is unlikely to result in misclassification of patients where some are recorded as being alive only to die a few days later.

Being a pragmatic trial, the study will not interfere with any procedure, investigations, or treatments that the attending clinicians administer to participants. However, all treatments received will be recorded.

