### Sample size {14}

The primary hypothesis is that adjunct corticosteroid treatment will reduce mortality in the intervention arm by ~25% (relative measure). This is a conservative measure as the studies described in the background report relative risk reductions of between 33% and 61%. Observational data indicates 30% in-hospital mortality among based on data collected from CIN hospitals in the past one year and Kilifi County Hospital over a period of 5 years
^
24
^. We have made a conservative assumption that 30-day mortality in the control arm of the trial will be 20% and that 30-day mortality in the intervention arm will be 15%. Allowing for 5% loss to follow-up, a sample size of 1,090 patients per study arm (total 2,180 patients, ~ 390 deaths) will achieve statistical power of 85%, with a 2-sided type 1 error rate of 5%.

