## Assignment of interventions: allocation

### Sequence generation {16a}

Once eligibility has been confirmed and informed consent provided, all patients will be randomized to receive either:

a) Standard of care, OR,

b) Standard of care plus adjunctive low-dose corticosteroids for 10 days

The random allocation sequence will be computer-generated at the KEMRI-Wellcome Trust Research Programme according to a block randomization list of random block sizes for each site.

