### Methods for additional analyses (e.g. subgroup analyses) {20b}

Secondary analyses will be conducted as for the primary analysis but adjusting for the confounding factors of gender, hospital location, age at randomization and any other confounder as deemed appropriate. Although randomization into the study is not stratified by any of the baseline characteristics, stratified analyses will be presented if there is significant evidence of interaction by any of the baseline variables.

The safety analysis will be based on the safety population, that is, all participants who received a study treatment.

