### Methods in analysis to handle protocol non-adherence and any statistical methods to handle missing data {20c}

During the data collection process, efforts will be made to minimize missing data occurrence. Should missing data occur, the numbers (with percentages) of losses to follow-up (defaulters and withdrawals) will be reported by randomized group at each assessment time point. If possible reasons why the data are missing will also be reported. Missing data will not be imputed in anyway.

The primary analysis will be based on an intention-to-treat (ITT) population. An unadjusted analysis of the primary outcome will also be performed on the per-protocol (PP) population. This will exclude patients stopping or pausing the study medication at any time point and those withdrawn from the trial.

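### The primary Cox model depends on whether baseline imbalance is observed; one fixed model, with site in it by design, should replace the trigger

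*Protocol article*

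**What the plan says.** Four places in the Protocol article bear on which model gives the primary result.

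- Section {20a} sets the default for 30-day mortality: "we will use the unadjusted hazard ratio determined from Cox regression to estimate the mortality rate ratio between the treatment groups".
- The same section then sets the condition, "If we detect any imbalances in potential confounders at baseline (such as age, sex, severity of illness, study site", and the consequence: "then an adjusted Cox model will be used". It does not say what counts as an imbalance, the list of factors is illustrative, and it is not stated whether the adjusted result replaces the unadjusted one or stands beside it.
- Section {20b} describes secondary analyses that follow the primary analysis but differ in "adjusting for the confounding factors of gender, hospital location, age at randomization and any other confounder as deemed appropriate". That contrast makes sense only if the primary analysis is unadjusted.
- Section {20c} plans the per-protocol comparison without covariates: "An unadjusted analysis of the primary outcome will also be performed on the per-protocol (PP) population".

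On the design, section {16a} generates allocation "according to a block randomization list of random block sizes for each site". Sections {16c} and {17a} say that the trial is open-label.

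**The concern.** With sound randomisation, any baseline difference between the arms is chance. The reason to adjust for a factor is that it predicts death, not that it happens to look uneven. A rule keyed to observed imbalance can therefore adjust for an unimportant factor and leave out an important one.

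Three consequences follow.

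1. The trial does not have one primary result defined in advance. Two hazard ratios are candidates, and the step between them rests on a judgement made with open-label data in hand.
2. The sections do not fit together. If the trigger fires, the intention-to-treat result would be adjusted and the per-protocol result unadjusted. Section {21b} tests the primary outcome at the interim by Cox regression without saying which model, so the interim and final tests could differ too.
3. Site is treated the wrong way round. Blocking within site keeps the arms close to balance at each site, so site is very unlikely to trigger adjustment. Yet it is the one factor that the allocation respects and that the analysis should reflect.

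**Working it through.** **Inputs from section {14}.** 30-day mortality 20% (control) and 15% (intervention); two-sided 5%; 85% power; 5% loss; 1,090 per arm. Section {8} gives 1:1 allocation. The documents give no test for imbalance and no prognostic strength for any covariate, so both are assumed below.

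**1. The plan's own figure.** Two proportions, pooled variance under the null, no continuity correction:

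n = [1.960·√(2·0.175·0.825) + 1.036·√(0.20·0.80 + 0.15·0.85)]² / 0.05² = (1.053 + 0.556)² / 0.0025 ≈ 1,036 per arm.

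With 5% loss: 1,036 / 0.95 ≈ 1,091, against 1,090 stated. At 1,090 × 0.95 = 1,035.5 analysed per arm, power is 85.0%.

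Check on the Cox scale: HR = ln 0.85 / ln 0.80 = 0.728; deaths = 1,035.5 × 0.35 = 362; z = 0.317 × √362 / 2 − 1.960 = 1.06, power 85.5%. The trial is sized for an unadjusted comparison and reaches its target with one.

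**2. How often chance alone would switch the model.** For k independent tests at level a, the probability of at least one imbalance is 1 − (1 − a)^k.

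- Three named factors other than site (age, sex, severity): 1 − 0.95³ = 14.3%; at a = 0.10, 27.1%.
- A longer list, for example k = 10: 40.1%; at a = 0.10, 65.1%.

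Site is left out of the count because blocking holds it near balance.

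**3. Effect on error and power.** Simulated Cox analyses of 2,071 patients (2,180 × 0.95), with marginal risks of 20% and 15% (20% in both arms under the null), four independent normal baseline covariates and 8,000 trials per scenario. The rule was applied with a 5% test on each covariate. The assumed SD of the covariates' combined log-hazard score is in the first column.

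| SD | Power, unadjusted | Power, rule, imbalanced factors only | Power, rule, all four once triggered | Power, always adjusted | Type I error, rule | Type I error, free choice of result |
|---|---|---|---|---|---|---|
| 0.5 | 85.1% | 85.4% | 85.5% | 87.0% | 4.9–5.0% | 6.4% |
| 0.8 | 85.5% | 86.0% | 86.5% | 90.1% | 4.9% | 7.0% |
| 1.0 | 85.3% | 86.2% | 87.2% | 91.8% | 4.5% | 6.9% |

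Monte Carlo standard error is about 0.4 points or less. Always adjusting gains about 1.5 points over the rule at SD 0.5 and up to about 5.5 at SD 1.0. The simulation has four covariates that can trigger and no site effect, so it indicates scale only.

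**4. The two hazard ratios differ.** Under the same 20% and 15% risks, the hazard ratio conditional on the covariates is 0.722, 0.711 and 0.700 at SD 0.5, 0.8 and 1.0, against 0.728 unadjusted. The gap is small, but the two are not the same quantity.

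**5. What missing covariates would cost.** Section {18a} takes clinical data from medical records, and section {20c} rules out imputation. If a covariate were missing for 5% of patients (assumed) and they dropped out of the model, the 87.0% would become: (1.960 + 1.126)·√0.95 − 1.960 = 1.05, or about 85%. At the weakest assumed prognostic strength the gain is gone.

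**The case against.** The best defence is that the adjusted model is only a supplement. Section {20b} treats the primary as unadjusted and already plans an analysis with sex, hospital and age, and section {20c} keeps the per-protocol analysis unadjusted. An analysis plan that is not shown may define imbalance, list the covariates and settle which result leads. This carries weight: the absence of those details from an article is not a fault. What remains is the conditional sentence in {20a}, which states a data-dependent rule and does not call the adjusted model supplementary. The sections need reconciling.

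Stronger readings are tempting but not supported.

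- *The rule inflates type I error.* The text conditions on baseline imbalance, not on the result. Followed mechanically, it gives 4.5 to 5.0%. The 6.4 to 7.0% describes an analyst who reports whichever model is significant. The undefined trigger leaves room for that, but the text does not authorise it.
- *Planned power is lost.* The 85% reproduces without adjustment. What is forgone is a gain that the plan never claimed, and its size rests on assumed prognostic strengths.
- *Nearly one trial in five would switch.* That figure (1 − 0.95⁴ = 18.5%) counts site among the four named factors, although blocking makes a site imbalance very unlikely.
- *The primary covariate list extends to whatever is deemed appropriate.* That phrase belongs to the secondary analyses in {20b}. The primary rule is open only through its illustrative list.

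It can also be said that an unadjusted primary analysis is valid, and that adding a severity covariate from routine records could drop patients. Both points stand and shape the fix.

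**Conclusion.** The concern holds in limited form. Section {20a} lets observed imbalance, judged by no stated criterion, choose the primary model, and {20b} and {20c} presume a different answer. The main harm is that the primary result of an open-label mortality trial is not uniquely fixed in advance; this needs no simulation. The switch would occur by chance in about 14% of trials under 5% tests on the three factors other than site, and more often with a looser test or a longer list.

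The rule itself does not breach the 5% level, and the trial is not underpowered because of it. The efficiency argument is secondary: roughly 1.5 to 5.5 points of power, given covariate scores with SD 0.5 to 1.0 and complete covariate data. This is a wording defect to correct before the analysis, not a threat to the trial's validity.

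**What to change.** In section {20a}, delete the imbalance condition and state one primary model: Cox regression stratified by site and adjusted for age and sex, whatever balance is observed. Add a baseline severity measure only if it is named and either recorded for essentially all patients or covered by a missing-covariate rule that keeps every randomised patient in the intention-to-treat analysis. Such a rule would need an exception to the ban on imputation in {20c}. Always report the unadjusted hazard ratio as supporting. Use the same model at the interim and final analyses, as far as timing still allows. In {20b}, replace the open-ended clause with the same fixed covariates.

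Timing matters. The study status section puts the end of recruitment at 30 June 2024, so 30-day follow-up was over well before the article appeared on 28 May 2025. The documents do not say whether outcomes by arm have been seen, although {21b} sends interim results to the data safety monitoring board and the steering committee. The plan should record that those who fixed the model had not seen outcomes by arm. If that can no longer be said, keep the unadjusted hazard ratio as the sole primary result and always report the fixed adjusted model as a sensitivity analysis.

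The cost is wording only, with no change to patients or procedures. The downside of the adjusted primary is that its hazard ratio is conditional (about 0.70 to 0.72 against 0.728 in the scenarios above) and must be described as such.

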### Criteria for discontinuing or modifying allocated interventions {11b}

During participation, the trial intervention may be stopped, and the participant withdrawn for the following reasons:

The participant’s attending physician may withdraw the study drug in those randomized to the intervention arm due to side effect/s or if the corticosteroids seem to cause worsening of a participant’s existing condition(s). Additionally, they may recommend administration of corticosteroids to a participant randomized to the control arm if in their opinion such a participant requires a corticosteroid as part of their care. Changes in treatment and reasons for change will be captured into the database in such casesIf a participant tests positive for COVID-19 after joining the trial and undergoing randomization, they will be withdrawn from the trial. This is because there will no longer be meeting the eligibility criteria, in addition to loss of equipoise since they will require to be on corticosteroids.If a participant requests to be withdrawn from the trial and was in the intervention arm, the corticosteroids will be discontinued and the participant withdrawn from the trial.

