### Strategies to improve adherence to interventions {11c}

While in-patient, trial staff will review all participants daily and ensure they are adherent to their prescribed medication, both standard care and corticosteroids where relevant. At discharge, participants will be advised to complete their medication as prescribed. Because of the pragmatic nature of the trial, trial staff will not conduct any procedures to monitor and/or improve adherence to treatment after discharge.

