### Interim analyses {21b}

An interim analysis will be conducted after half of the anticipated sample has been enrolled and completed their final visit. Statistical considerations for ending the trial prior to reaching the target enrollment will be based on the Haybittle-Peto stopping rules for the primary outcome
^
28
^.

The analysis will explore the primary outcome i.e., to determine the effect of adjunctive corticosteroids on all-cause mortality at 30 days after randomization in both the intention-to-treat (ITT) and per protocol (PP) participants. Cox regression will be used to test for differences in the rates of the primary outcome by randomization arm. The proportional hazards assumption will be evaluated graphically and using formal statistical tests. Kaplan-Meier survival curves will be constructed to display cumulative mortality over the 30-day follow-up period.

The results of this analysis will be shared with the trial’s Data Safety Monitoring Board (DSMB) and Trial Steering Committee (TSC) who will advise on continuation of the trial based on clear survival benefits or futility.

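### The per-protocol set is defined by stopping a drug that only the intervention arm takes, so its unadjusted mortality comparison is biased in a direction that cannot be known in advance

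*Protocol article*

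**What the plan says.** The primary analysis in section {20a} of the protocol article is by intention to treat. The same section defines a second population: "In the per-protocol analysis we will exclude patients stopping or pausing the study medication at any time point and those withdrawn from the trial". Section {20c} repeats this rule and specifies an unadjusted analysis of the primary outcome in that population.

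Section {11b} shows whom the rule can reach. The attending physician "may withdraw the study drug in those randomized to the intervention arm due to side effect/s" or because the drug seems to make an existing condition worse. For the other arm, "they may recommend administration of corticosteroids to a participant randomized to the control arm" if they judge it necessary. Such changes and their reasons are recorded. Neither per-protocol statement names a control patient's receipt of corticosteroids as a deviation.

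On adherence, section {11c} has trial staff review patients daily in hospital, but "trial staff will not conduct any procedures to monitor and/or improve adherence to treatment after discharge". The trial design section gives a median stay of 4 days, against a 10-day course. Section {13} adds phone calls on days 14 and 30 that ask about medication received.

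At the interim, section {21b} examines 30-day mortality "in both the intention-to-treat (ITT) and per protocol (PP) participants" and sends the results to the DSMB and the TSC. It names the population without saying whether that analysis is adjusted.

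**The concern.** Controls have no study medication to stop, so they can leave the per-protocol set only as withdrawals (for example after a positive COVID-19 test, which can happen in either arm). The stopping criterion acts on the intervention arm alone, after randomization, and the physician's stated reasons are tied to how the patient is doing. What remains is a selected intervention arm set against an almost unselected control arm, with no adjustment for the selection.

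At stake is how a supportive result will be interpreted. A per-protocol estimate that differs from intention to treat is easily taken as the effect of actually taking the drug. Here the difference could come entirely from who was removed. The same population is put before the committees that advise on continuation.

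**Working it through.** **Inputs from section {14}.** The plan assumes that "30-day mortality in the control arm of the trial will be 20"% and that "30-day mortality in the intervention arm will be 15"%, with 1,090 patients per arm, 85% power and a two-sided 5% level. "Allowing for 5% loss to follow-up" is the attrition term.

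**Step 1: reproduce the plan's figure.** With the uncorrected pooled formula,
n = [1.960·√(2·0.175·0.825) + 1.036·√(0.20·0.80 + 0.15·0.85)]² / 0.05² = 1,036 per arm after rounding up. Dividing by 0.95 gives 1,090.5, against the stated 1,090. The design figure reproduces.

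**Step 2: effect of the exclusion under no true effect.** Let both arms have 20% mortality. Let a share f of the intervention arm stop or pause, with mortality m among them. Neither f nor m is in the documents; both are assumed. Then

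per-protocol intervention mortality = (0.20 − f·m)/(1 − f), and RR = that value / 0.20.

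The bias is zero only when m = 0.20. After 5% loss there are 1,090 × 0.95 = 1,035.5 controls and, at f = 10%, 932 intervention patients. The last two columns use a two-sided 5% two-proportion test, which nominally gives 2.5% in each direction.

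| f | m | Per-protocol intervention mortality | RR | Chance of significant benefit | Chance of significant harm |
|---|---|---|---|---|---|
| 10% | 10% | (0.20 − 0.01)/0.90 = 21.1% | 1.06 | 0.5% | 8.9% |
| 10% | 20% | (0.20 − 0.02)/0.90 = 20.0% | 1.00 | 2.5% | 2.5% |
| 10% | 30% | (0.20 − 0.03)/0.90 = 18.9% | 0.94 | 9.0% | 0.5% |
| 10% | 40% | (0.20 − 0.04)/0.90 = 17.8% | 0.89 | 24% | 0.1% |
| 10% | 50% | (0.20 − 0.05)/0.90 = 16.7% | 0.83 | 48% | <0.1% |

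The effect scales with f. At m = 40%, RR is 0.95 for f = 5% and 0.75 for f = 20%. The latter is 15.0% against 20%, the whole design effect. At m = 10% and f = 20%, RR is 1.125. The plan uses a hazard ratio. Under constant hazards, ln(1 − p)/ln(0.80) gives 1.06, 1.00, 0.94, 0.88 and 0.82 for the five rows, so the conclusion is the same.

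**Step 3: which side of 20% is m likely to fall?** Stops in hospital for worsening suggest m above 20%. Two things push the other way. A patient must be alive to stop, and patients who stop after discharge have already survived the admission. In a null simulation with deaths weighted to the early days and about 10% assigned to stop between days 1 and 10, stopping unrelated to risk gave RR about 1.04. Stopping by lower-risk patients gave 1.08, and stopping moderately related to higher risk gave 0.99.

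**Step 4: would excluding control crossovers cure it?** Take f = 10%, m = 40% (RR 0.889). Also dropping 5% of controls with 40% mortality gives control mortality (0.20 − 0.02)/0.95 = 18.95%, and RR = 17.78/18.95 = 0.938. RR returns to 1.000 only if the control exclusions match exactly (10% with 40% mortality). Dropping those 5% of controls with no intervention exclusions gives 20/18.95 = 1.056, an apparent harm. Keeping crossovers leaves control mortality at 20% under the null and adds no bias.

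**The case against.** The strongest reply is that intention to treat is plainly primary, that the per-protocol analysis is only additional, and that nothing here can move the primary estimate. This stands and limits the weight of the point. It does not repair a population and an unadjusted method that the protocol itself fixes, in two sections.

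A reader might infer that the rule manufactures a steroid benefit. The documents do not support that. They give no mortality for patients who stop; section {11b} lists side effects and participant request as well as worsening; and the day-14 and day-30 calls can reveal later stops among survivors. Benefit is the likelier direction for in-hospital stops due to worsening, but not for the set as a whole.

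A reader might also infer that keeping control patients who received corticosteroids creates false benefit. Under no true effect it does not (Step 4). Whether they are kept is itself unclear: the sentence allowing corticosteroids in controls sits under an opening line in {11b} that speaks of participants being withdrawn, and the per-protocol rule removes those withdrawn.

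A much larger bias would follow if deaths during the 10-day course were coded as stopping. Section {11b} does not list death as a reason for stopping, and the abstract and Table 2 describe treatment for up to 10 days. That reading is not needed and is not relied on here.

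Finally, section {21b} ties the Haybittle-Peto rule to the primary outcome, whose primary analysis is intention to treat, and a DSMB charter exists that is not shown. So the documents do not say that the per-protocol result can trigger stopping. They do say that the committees will see it.

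**Conclusion.** The point holds as a defect in a supportive analysis. The exclusion for stopping or pausing falls on one arm, acts after randomization, is linked to clinical course, has no named control counterpart and is analysed without adjustment. The estimate is therefore biased by an amount and in a direction that cannot be known in advance. With 10% stopping and no true effect, the risk ratio ranges from 1.06 to 0.83 as stoppers' mortality runs from 10% to 50%, and the chance of a nominally significant benefit runs from 0.5% to 48%. These figures rest on the plan's 20% control mortality and 5% loss, and on assumed stopping rates and stoppers' mortality. The primary conclusion is not threatened. The definition should still be corrected before the final analysis is reported.

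**What to change.** - Define deviations for both arms, for analysis purposes only. Intervention: corticosteroid stopped or paused for a reason other than death. Control: a systemic corticosteroid started. State that death on allocated treatment is not a deviation.
- Reconcile the opening line of {11b} on withdrawal with the per-protocol rule in {20a} and {20c}, so that it is clear whether a control patient given corticosteroids counts as withdrawn.
- Replace exclusion with censoring at the deviation, weighted by the inverse probability of remaining adherent. Use baseline data, the daily in-patient records and the phone-call medication data, all already collected. Symmetric exclusion alone is not enough (Step 4).
- Label the analysis supportive, and state that intention to treat alone governs the stopping boundary and the trial's conclusion.

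The cost is analysis-plan wording and some programming, a wider confidence interval, and reliance on an adherence model. That model will be weakest after discharge, where there are only two calls and no adherence monitoring. Recruitment closed on 30 June 2024, so the interim wording may no longer have practical effect; the other changes still bear on the final report.

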## Objectives {7}

Primary Objectives

To determine if there is a difference in the proportion of patients with community acquired pneumonia that die within 30 days of being randomized to receive adjunctive corticosteroid treatment compared to those that are randomized to receive standard treatment only

Secondary Objectives

To determine if there is a difference in the proportion of patients with community acquired pneumonia that die within seven, 14 and 21 days of being randomized to receive adjunctive corticosteroid treatment compared to those that are randomized to receive standard treatment onlyTo determine if there is a difference in the proportion of patients with community acquired pneumonia that die in hospital and out of hospital after being randomized to receive adjunctive corticosteroid treatment or standard treatment for community acquired pneumonia onlyTo determine the correlation of pre-existing and treatment induced changes in the participants’ immune and metabolic profiles with study outcomes by trial arm

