### Participant timeline {13}

All participants enrolled in the trial will be reviewed once daily while in-patient by a member of the study team. During these reviews, data on clinical progress will be recorded. The data collected will include documentation of antibiotics and other treatments that the patient is receiving.

After discharge, a member of the study team will make a phone call to the participant or their next of kin (where a participant is not reachable on their personal phone) on day 14 and day 30 post randomization to find out how the patient is doing including whether readmitted to a hospital, fully recovered or if the participant has died.

During the telephone follow-up, data on the results of any additional tests performed and/or medications received after the hospitalization will also be collected. If the patient is reported to be deceased, the date of death and cause of death (where available) will be recorded.

There will be no further follow up after day 30 post randomization into the study.

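### Complete-case analysis of 7-, 14- and 21-day mortality discards lost patients' known follow-up that the primary analysis keeps; the bias is small, conditional and easily avoided

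*Protocol article*

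**What the plan says.** All references are to the protocol article.

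- **Secondary endpoints.** Statistical methods {20a}: "Complete case analyses will be used for secondary endpoints". Effects are to be estimated "using linear, logistic, or cox proportional hazards regression as appropriate". No model is fixed for mortality at days 7, 14 and 21. Objectives {7} frames these outcomes as a "difference in the proportion of patients with community acquired pneumonia that die within seven, 14 and 21 days".
- **Primary endpoint.** In the same section, in the text on 30-day mortality: "If losses to follow-up do occur, patients will be censored at time of last assessment". Kaplan-Meier curves over the 30 days are also planned.
- **Additional analyses {20b}:** "Secondary analyses will be conducted as for the primary analysis but adjusting for the confounding factors of gender, hospital location, age at randomization".
- **Missing data {20c}:** "Missing data will not be imputed in anyway". Withdrawals are counted among losses to follow-up.
- **Follow-up.** Trial design {8}: "The median duration of hospital admission for patients with CAP in the participating hospitals is 4 days". After discharge, Participant timeline {13} schedules telephone calls "on day 14 and day 30 post randomization to find out how the patient is doing", with the date of death recorded if the patient has died.

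**The concern.** One set of death dates is given two missing-data rules. Take a patient discharged alive on day 4 and never reached again. The primary analysis counts that patient as at risk until last assessment. A binary complete-case analysis at day 7, 14 or 21 leaves the patient out altogether. A patient who died in hospital on day 3 is kept in both.

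Two things are at stake. The day-7, -14 and -21 results would rest on a subset of the randomised patients and would not lie on the same mortality curve as the day-30 result. And because the trial is open label, with outcomes after discharge collected by telephone, loss could differ by arm. The comparison would then shift in a direction set by which arm lost more.

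**Working it through.** **1. The plan's own figure.** Sample size {14} gives 20% against 15% 30-day mortality, 85% power, two-sided 5% and 5% loss. The two-proportion formula gives 1,036 per arm, and 1,036 / 0.95 = 1,091, against 1,090 stated. Expected deaths are (0.20 + 0.15) × 1,090 = 381.5, against about 390 stated. The design inputs reproduce closely, so they are used below.

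**2. Who is dropped.** A patient discharged before day 7 and never reached is unknown at all three days. One reached on day 14 but not on day 30 is complete for days 7 and 14 and unknown only at day 21. One reached on day 30 is complete throughout, provided any death is dated. Day 21 is therefore the most exposed.

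**3. Size by algebra.** Let p be the true risk by the day in question, l the share of randomised patients with unknown status, and q the death risk of those patients between last contact and that day. Deaths seen are p − l·q and known statuses are 1 − l, so

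complete-case risk = (p − l·q) / (1 − l), and bias = l·(p − q) / (1 − l).

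The bias is upward only if q < p. With p = 20% (control) and 15% (intervention):

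| Loss, control / intervention | q, control / intervention | Complete-case risks | Risk ratio | Difference (points) |
|---|---|---|---|---|
| 5% / 5% | 0 / 0 | 21.1% / 15.8% | 0.75 | −5.3 |
| 5% / 5% | 10% / 7.5% | 20.5% / 15.4% | 0.75 | −5.1 |
| 5% / 5% | 20% / 15% | 20.0% / 15.0% | 0.75 | −5.0 |
| 5% / 5% | 30% / 22.5% | 19.5% / 14.6% | 0.75 | −4.9 |
| 3% / 7% | 0 / 0 | 20.6% / 16.1% | 0.78 | −4.5 |
| 7% / 3% | 0 / 0 | 21.5% / 15.5% | 0.72 | −6.0 |

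The largest overstatement at 5% loss is 0.05 × 0.20 / 0.95 = 1.05 points. Only the 5% overall loss comes from the protocol. The split by arm and q are assumptions.

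**4. Simulation on the call schedule** (4 million per arm; median stay 4 days; loss independent of death; half of the lost reached on day 14 but not day 30, the rest last seen at discharge). Control-arm risks with front-loaded deaths and about 5.4% loss per arm:

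| Day | True | Complete case | Kaplan-Meier |
|---|---|---|---|
| 7 | 10.2% | 10.4% | 10.2% |
| 14 | 14.1% | 14.3% | 14.1% |
| 21 | 17.0% | 17.6% | 17.0% |

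The excess is about 0.15, 0.20 and 0.58 points. With a constant death hazard it is 0.06, 0.09 and 0.36 points. The risk ratio moves by no more than 0.001.

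Unequal loss, front-loaded deaths, risk ratio as true / complete case / Kaplan-Meier:

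- 2.7% control, 8.2% intervention: day 14, 0.744 / 0.755 / 0.744; day 21, 0.747 / 0.775 / 0.747.
- 8.0% control, 2.7% intervention: day 14, 0.743 / 0.733 / 0.743; day 21, 0.746 / 0.721 / 0.746.

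**5. Simulation with every loss at discharge** (2 million per arm; in-hospital hazard assumed 5 times the later hazard). Here loss coincides with a fall in risk, so it is no longer independent of risk. At day 14, true / complete case / Kaplan-Meier:

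- 5% / 5%: control risk 13.8 / 14.2 / 14.0%; risk ratio unchanged.
- 7% / 3%: risk ratio 0.743 / 0.722 / 0.734.
- 3% / 7%: risk ratio 0.743 / 0.764 / 0.751.

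Censoring removes roughly half of the bias or more, but not all of it.

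**6. Against sampling error.** Take day-14 risks of 13.7% and 10.2% and 0.95 × 1,090 ≈ 1,035 patients per arm. The standard error of the log risk ratio is √[0.863/(0.137 × 1,035) + 0.898/(0.102 × 1,035)] ≈ 0.12. The move from 0.743 to 0.722 is ln(0.743/0.722) ≈ 0.03, about a quarter of a standard error.

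**The case against.** The strongest reply is that the protocol does not clearly exclude these patients. Cox regression is among the permitted models, and a patient with a known last-contact date has usable data in a Cox model. {20b} also says that secondary analyses follow the primary. And the planned Kaplan-Meier curves already give censored risks at days 7, 14 and 21.

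Part of this stands. The exclusion follows from a binary reading, and the text does not settle the model. But the complete-case sentence is an explicit rule for all secondary endpoints, the menu of models does not lift it, and objectives framed as proportions lead naturally to a binary analysis. The {20b} sentence sits under additional analyses. If it does cover these endpoints, it conflicts with {20a}. The curves would show the risks, but the planned effect estimates and confidence intervals would still come from complete cases.

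A reader might infer that early mortality is bound to be too high in both arms. The documents do not support that. It requires q below p, and they say nothing about the risk of lost patients. Nor are all losses patients discharged alive: {20c} counts withdrawals, and {11b} provides for withdrawal on request or after a positive COVID-19 test, either of which can happen in hospital. The day-14 call, next-of-kin contact and the three contact details collected per patient also limit how many are unknown at days 7 and 14.

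**Conclusion.** The point holds as a modest weakness of method, confined to secondary endpoints. The complete-case rule discards follow-up that the primary analysis of the same dates uses. If lost patients' later risk is below the cumulative risk, mortality at the planned 5% loss is overstated by at most about 1 point at a 20% risk, and by about 0.1 to 0.6 points in the simulations. Day 21 is worst when the day-14 call is modelled.

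A reader might also infer a biased treatment comparison. With equal loss there is essentially none. With unequal loss the risk ratio shifts by about 0.02 to 0.03 at day 21, or at day 14 if every loss occurs at discharge. On the call schedule the day-14 shift is only about 0.01. The direction depends on which arm loses more, and the protocol gives no split by arm. The 30-day result is untouched.

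**What to change.** In {20a}, replace complete-case analysis for mortality at days 7, 14 and 21 with the primary method truncated at each day:

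- include all randomised patients, censored at the last date known alive;
- report Kaplan-Meier risks by arm with the Cox estimate;
- count any later contact, such as the day-30 call, as proof of survival at the earlier days;
- keep complete case as a sensitivity analysis, and report loss by arm beside it.

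Reconcile {20a} with {20b} so that one rule governs these endpoints. State that censoring assumes loss unrelated to risk and will not fully correct loss that clusters at discharge.

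The cost is a sentence or two of analysis text, using the primary analysis dataset and code, with no new data. Study status gives the end of recruitment as 30 June 2024, so the change should be dated and recorded as made after that.
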